### Measurement period

In the context of the intervention study, the incontinence-affected individuals included are accompanied over a system test period of four months. The measurements will take place exclusively in the respective inpatient care facility. For better supervision by the study management, the measurements should be carried out in a maximum of two facilities in parallel during the project period. The measurements will be carried out exclusively by the study staff of the University of Applied Sciences Neubrandenburg.

A total of seven measurement points are planned for the participants of the primary target group. One measurement will take place at the start (t0) and one at the end (t6) of the four-month study period. Between these two points (t0 and t6), the quantitative surveys will be conducted every three weeks (t1, t2, t3, t4, t5). If necessary, when taking the measurements, the study staff of the Neubrandenburg University of Applied Sciences may be assisted by the nursing staff of the relevant inpatient nursing facility (e.g. if a participant has a greater cognitive impairment).

Four measurement points are planned for the individuals of the secondary target group. One measurement will take place at the beginning (t0) and one at the end (t3) of the four-month study period. In the meantime, the qualitative and quantitative surveys will take place every six weeks (t1, t2) (see Fig. 3 and Table 2).

**Fig. 3 Fig3:**

Scheduling of the measurements by target group

**Table 2 Tab2:** Outcomes, measurement tools and follow-ups [11, 36, 39–43, 46–50]

Primary outcome	Measurement tool	t0	t1	t2	t3	t4	t5	t6
Cognitive ability	MMSE [36]	X						
Incipient falls	STRATIFY [39, 40]	X	X	X	X	X	X	X
	Tinetti Test [41]	X	X	X	X	X	X	X
	Risk factors as per DNQP expert standard [11]	X	X	X	X	X	X	X
	Analysis of fall records [42]	X	X	X	X	X	X	X
**Secondary outcomes**	**Measurement tool**	**t0**	**t1**	**t2**	**t3**	**t4**	**t5**	**t6**
Quality of life	FLQM [43]	X	X	X	X	X	X	X
Sleep quality and disruptions of sleep	KSS	X	X	X	X	X	X	X
	RCSQ [46–50]	X	X	X	X	X	X	X
Consumption of incontinence material	Documentation	X	X	X	X	X	X	X
General health	Nursing documentation	X	X	X	X	X	X	X
Effects	Qualitative interview	X	X	X	X			
Experience	Qualitative interview	X	X	X	X			
Acceptance	Qualitative interview	X	X	X	X			
Changes to workflows	Qualitative interview	X	X	X	X			
Technology affinity	TA-EG (modified)	X	X	X	X			

### Power calculation

The sample size calculation is based on the RCT by Chittrakul et al. [51] in which a special exercise program for fall prevention to avoid falls and increase the quality of life was developed. The result of the RCT was that the participants in the IG fell on average 1.13 times (SD = 0.84) and in the CG the average was 2.22 [51]. For the current sample size calculation, a more conservative estimate was made (M = 1.65) since a less intensive intervention is to be studied that is nevertheless of high clinical relevance. To detect a significant difference between the two groups in a two-arm test with a significance level of 0.05 and 80% power, we need at least 34 persons in each group. Thus, a total of at least 68 persons will be included. Due to the high vulnerability of the sample and assuming a drop-out rate of about 15%, a total of 80 indiviudals will be included with 20 participants from each nursing facility (primary target group). The participants will be divided into an intervention group and a control group.

Concerning the nursing staff, as secondary target group, about six to eight individuals in each inpatient facility, who are responsible for the incontinence care of the participants in the primary target group and routinely use the assistance system in their daily professional practice will be recruited. The sampling of nursing staff follows a qualitative approach and aims to ensure the representativeness of the target group [38] by contrasting characteristics such as gender and professional experience.

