### Inclusion criteria

#### Primary target group

To consider the different comorbidities of the primary target group and to be able to realistically assess the benefits of the digital assistance system, the inclusion criteria were defined relatively broadly. Individuals included in the RCT:have a moderate to severe incontinence (degree of severity ≥ 2, urinary or urinary and faecal incontinence) andhave given their written informed consent to participate in the RCT after receiving information and clarification. If individuals are not able to consent to study participation by themself due to cognitive impairments, their family caregivers or legal guardians may provide consent.

The severity of incontinence is determined by the consumption of incontinence material per person in need of care as recorded in the care documentation.

Due to the multifaceted occurrence of incontinence, other factors such as cognitive ability, mobility as well as the degree of care of the person affected do not play a role as criteria for study participation. Individuals who are cognitively impaired as well as not impaired; who are mobile as well as immobile; and who have a high or low level of care will be included in the RCT.

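### The 80% power for falls at 34 per group rests on one arm's SD of 0.84 used for both arms at higher mean counts; the protocol's own figures, scaled to those means, give about 36% to 56%

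*Protocol article*

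**What the plan says.** Falls are the sole primary endpoint of the resident trial (Endpoints section). The Power calculation section of the protocol article takes its planning values from a cited randomised trial of an exercise programme, where "the participants in the IG fell on average 1.13 times (SD = 0.84) and in the CG the average was 2.22". Because the present intervention is judged less intensive, "a more conservative estimate was made (M = 1.65"). The section then states that "with a significance level of 0.05 and 80% power, we need at least 34 persons in each group", hence 68 in total, raised to 80 for about 15% drop-out.

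The section names no test and does not say which SD entered the formula. The only SD it prints is 0.84, attached to the cited intervention arm. It prints none for the control mean of 2.22 and none for the planned mean of 1.65. The inclusion criteria admit residents "who are mobile as well as immobile".

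**The concern.** The stated sample size depends on the SD as much as on the difference in means. The one SD available comes from the arm with the lowest mean (1.13) and appears to have been used for two arms with means of 1.65 and 2.22, the latter about twice as large.

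For counts such as falls per resident, the variance usually grows with the mean. Borrowing the SD of the low-mean arm then understates the spread in both planned arms and overstates power. The section offers no reason to expect so little variation, and enrolment regardless of mobility gives no reason to expect a homogeneous population.

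At stake is how the falls result is read. A non-significant difference in a trial described as 80% powered would carry more weight against the system than the data could justify.

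**Working it through.** **Inputs (Power calculation section).** Cited intervention arm: mean 1.13, SD 0.84. Cited control arm: mean 2.22, SD not given. Planned mean: 1.65. Alpha 0.05, power 80%, 34 per group. Two-sided testing is assumed, since sidedness is not stated.

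**Step 1: reproduce the plan's figure.** Difference = 2.22 − 1.65 = 0.57, common SD 0.84:

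n per group = 2 × (1.96 + 0.8416)² × (0.84 / 0.57)² = 34.09

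This matches the stated 34. Power at 34 per group is 79.9% by the normal formula and 78.7% by the t-test. Solving backwards from n = 34 and a difference of 0.57 gives SD 0.839. The drop-out step is also right: 68 / 0.85 = 80.

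**Step 2: what SD 0.84 implies.** Variance = 0.84² = 0.7056. A Poisson count has variance equal to its mean, so:
- at mean 1.65, Poisson SD = √1.65 = 1.28, and 0.7056 / 1.65 = 43% of Poisson variance;
- at mean 2.22, Poisson SD = √2.22 = 1.49, and 0.7056 / 2.22 = 32% of Poisson variance.

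The cited arm itself is below Poisson, but less so: 0.7056 / 1.13 = 0.624. Its coefficient of variation (CV) is 0.84 / 1.13 = 0.743.

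**Step 3: let the variance follow the mean.** Pooled SD = √[(variance at 1.65 + variance at 2.22) / 2]; difference 0.57; two-sided 5%; 34 per group. Power is from the t-test; n per group for 80% power is from the normal formula.

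| Variance assumption | Pooled SD | Power at 34 | n per group for 80% |
|---|---|---|---|
| 0.84 in both arms (reproduces the plan) | 0.84 | 79% | 35 |
| Variance/mean ratio 0.624 in both arms | 1.10 | 56% | 59 |
| Poisson in both arms | 1.39 | 38% | 94 |
| CV 0.743 in both arms | 1.45 | 36% | 103 |
| Intervention 0.84, control SD 1.0 | 0.92 | 71% | 42 |
| Intervention 0.84, control ratio 0.624 | 1.02 | 62% | 51 |
| Intervention 0.84, control Poisson | 1.21 | 48% | 71 |

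Worked example, second row: variances 0.624 × 1.65 = 1.030 and 0.624 × 2.22 = 1.386; pooled SD = √1.208 = 1.10; standardised difference = 0.57 / 1.10 = 0.52; power 56%.

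**Step 4: overdispersion (assumed values).** With negative binomial variance = mean + k × mean², power at 34 is about 22% for k = 0.5 and 16% for k = 1. The protocol gives no dispersion, so both values of k are assumptions.

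**Step 5: the same question as a rate ratio.** The planned ratio is 1.65 / 2.22 = 0.74. Under Poisson, SE of the log ratio = √[(1/2.22 + 1/1.65) / 34] = 0.176, giving 39% power, close to the t-test result. The ratio detectable with 80% power at 34 per arm, with the control mean held at 2.22, is about 0.59 under Poisson and about 0.48 at k = 0.5.

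**The case against.** The strongest defence is that the arithmetic is correct. The formula reproduces 34, the drop-out inflation reproduces 80, and what remains is a disputed variance assumption. The control-arm SD sits in a source not available here; if it and the SD at mean 1.65 were near 0.84, the stated power would stand. The only dispersion evidence in the protocol is below Poisson (variance 0.71 against mean 1.13). All of this is fair. It means that no single replacement figure can be claimed. It does not supply the missing SDs, and even the cited arm's own below-Poisson ratio brings power down to 56%.

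Some stronger readings are tempting but not supported:
- *That realistic power is 15% to 56%.* The low end needs a dispersion near 1, which the protocol does not give. The high end is not a ceiling: power is about 62% to 71% if the intervention SD stays at 0.84 and the control SD rises modestly.
- *That the mix of mobile and immobile residents fixes a lower power.* The inclusion criteria say only that mobility is not a criterion. No proportion of immobile residents is given, so any figure built on one would be invented.
- *That 1.65 might be the control mean.* The section justifies 1.65 by the weaker intervention, which bears on the intervention-arm mean, and the two-sided calculation reproduces 34 only on that reading. A comparison of 1.65 with 1.13 needs 41 per group two-sided by the same normal formula; it comes near 34 only one-sided (33). The sentence would benefit from naming the arm, but this is a matter of clarity.

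The choice of analysis model for falls may properly be left to an analysis plan. The point here concerns a calculation that the article itself publishes, with its inputs, N and power.

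**Conclusion.** The point stands as a defect in the basis of the power statement; the arithmetic is sound. The claim of 80% power at 34 per group depends on applying the lowest-mean arm's SD to two arms with higher mean counts, and the protocol offers no support for that.

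Carrying the protocol's own figures to the planned means gives about 36% (constant CV) to 56% (constant variance/mean ratio), with Poisson at 38%. Raising only the control-arm spread gives about 48% to 71% in the cases examined. Overdispersion would lower power further, to about 22% or 16% at the assumed dispersions of 0.5 and 1.

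These results assume two-sided testing at 5%, means of 2.22 and 1.65, and 34 evaluable residents per arm. Unless the unreported SDs are also close to 0.84, the trial is less well powered for its primary endpoint than stated, by an amount the protocol does not allow one to fix.

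**What to change.** Keep N = 80 and rewrite the power paragraph:
- state that 1.65 is the assumed intervention-arm mean, set against a control mean of 2.22, and that the test is two-sided;
- replace the single SD of 0.84 with either a documented control-arm SD and a justified SD at 1.65, or a rate-ratio calculation for counts over a stated range of variance assumptions, labelling any dispersion value as an assumption;
- replace the unqualified 80% with the resulting power range, and give the rate ratio detectable with 80% power at 34 per arm (about 0.59 under Poisson, against the planned 0.74).

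The cost is one paragraph and no additional residents. The downside is that the stated power becomes less favourable.

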### Recruitment

#### Primary target group

The recruitment procedure is divided into two phases: 1) The study staff of the Neubrandenburg University of Applied Sciences and those responsible from AssistMe will visit the participating inpatient nursing facilities. In an open event all residents of the facility who are interested will be informed about the RCT (including the aims of the study, procedure and the intervention). This is meant as opportunity to ask questions to the persons responsible for the RCT. This shall emphasise the absolute voluntary nature of study participation. 2) If the residents or their family caregivers/legal guardians indicate interest in participating in the study, they inform the responsible nursing staff in the facility. The nursing staff consolidate the interested parties and forward their names to the study staff at the Neubrandenburg University of Applied Sciences. The study staff then visits the interested parties again. In a conversation, they will be again informed in detail about the RCT as well as the intervention. In addition, the inclusion and exclusion criteria will be checked. Residents who meet the eligibility criteria and who would like to participate in the RCT are then examined regarding their cognitive performance using the Mini Mental Status Examination (MMSE). Depending on their score, they are assigned to the respective strata "cognitively impaired" or "not cognitively impaired." Subsequently, both subgroups are randomized individually into the intervention and control group.

Should individuals in the primary target group drop out of the RCT prematurely (e.g., due to compelling medical or nursing reasons), new particpipants will be recruited and included if they meet the inclusion criteria. This post-recruitment is foreseen up to a maximum of two months after the start of the system test period.

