### Endpoints

#### Endpoints of the primary target group (care recipients with urinary and faecal incontinence)

Occurring falls represent the primary endpoint of the RCT. Secondary endpoints include cognitive ability, quality of life, sleep quality and disruptions of sleep, incontinence material consumption and general health.

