### Group assignment

The aim is to ensure that IG and CG do not differ beyond the intervention with regard to the prognostic factor of the individuals' cognitive performance. Especially with a small sample size, a different approach could promote an unbalanced relationship between the two groups [31]. An independent researcher, who is not involved in the study, performs the allocation with the software Excel (version 2018) using a randomization list with simple random sampling. During this process, participants are also assigned a code (participant ID), under which they and their data are managed in the further course of the study.

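### Drop-outs may be replaced until halfway through a four-month period, so late entrants can have half the follow-up; this dilutes a comparison of fall counts and can bias it if replacements are unequal between arms

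*Protocol article*

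**What the plan says.** The Recruitment section (primary target group) says that when a resident drops out early, "new particpipants will be recruited and included if they meet the inclusion criteria". It then sets the limit: "This post-recruitment is foreseen up to a maximum of two months after the start of the system test period".

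The Measurement period section says that "the incontinence-affected individuals included are accompanied over a system test period of four months" and fixes the outer visits: "One measurement will take place at the start (t0) and one at the end (t6) of the four-month study period". Five visits at three-week intervals lie between them. No section gives a late entrant a separate four-month period.

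The endpoint is stated as "Occurring falls represent the primary endpoint of the RCT", and the Power calculation section works with mean falls per person. That section already allows for losses: "assuming a drop-out rate of about 15%, a total of 80 indiviudals will be included".

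On allocation, the paragraph before the replacement rule describes the eligibility check, MMSE and stratum, and ends: "Subsequently, both subgroups are randomized individually into the intervention and control group". The Group assignment section adds that an independent researcher "performs the allocation with the software Excel (version 2018) using a randomization list with simple random sampling". The Blinding section says that participants, nursing staff, system provider and study staff all know the assignment.

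**The concern.** A resident who joins at month two of a four-month period has half the time in which to fall. If falls are compared as counts per person, that resident is expected to contribute half the count for reasons unrelated to the intervention. Two things follow.

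First, if late entrants are spread evenly over the arms, both means fall in proportion and the absolute difference shrinks. Replacement then restores the headcount without restoring the information.

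Second, if one arm has more late entrants, its mean fall count drops more, and a difference appears with no true effect. This is conceivable because the trial is open and only the intervention group wears the device. The Possible harms section itself mentions pressure discomfort still under test and a feeling of being monitored. The replacement sentence asks only that inclusion criteria are met. It does not say that a newcomer goes through the randomisation list and does not rule out filling the vacated place. Nursing staff, who know the assignments, collect and forward the names of interested residents.

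Two of the methods in the Statistical methods section, repeated-measures MANOVA and chi-squared tests, do not in standard form handle unequal observation time.

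**Working it through.** **Inputs from the protocol.** Replacement window 2 months; period 4 months; cited trial 1.13 falls (SD 0.84) against 2.22; planning mean 1.65; 34 per group, 68 in total, 80 after allowing 15% drop-out.

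**The plan's own figures.** n per group = 2 × (z for alpha + z for power)² × SD² / difference², with alpha 0.05, power 80% and SD 0.84. The protocol does not say which arm 1.65 belongs to, or whether the test is one- or two-sided.
- Difference 2.22 − 1.65 = 0.57: 35 two-sided (34.1 before rounding up), 27 one-sided.
- Difference 1.65 − 1.13 = 0.52: 41 two-sided, 33 one-sided.

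The stated 34 is thus matched closely by 0.57 two-sided or 0.52 one-sided. The inflation is exact: 68 / 0.85 = 80.

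**Follow-up of the last replacement.** 4 − 2 = 2 months, or 50%. With visits every three weeks, t3 falls at week 9, so a month-two entrant has at most t3 to t6, four of seven visits.

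**Assumptions for the rest.** 40 per arm analysed after replacement; 12 replacements in total (15% of 80); all enter at month two; drop-outs' own data left out; the planning mean applies to four months (the protocol does not give the cited trial's follow-up).

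**Balanced replacement, 6 and 6.** Exposure share per arm = (34 + 6 × 0.5) / 40 = 0.925. The difference becomes 0.52 × 0.925 = 0.481. The ratio of means stays at 1.13 / 1.65 = 0.685. With SD held at 0.84, two-sided power at 40 per arm falls from 79% to 73%. For comparison, 34 full-length residents per arm with no replacements give 72%, so on raw counts the half-length replacements recover almost nothing.

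**Unequal replacement, no true effect.** False difference = control mean × (difference in exposure share). The last column uses the other reading of the planning figures.

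| Split IG/CG | Exposure IG, CG | Mean 1.65 (share of 0.52) | Mean 2.22 (share of 0.57) |
|---|---|---|---|
| 6/6 | 0.925, 0.925 | 0 | 0 |
| 8/4 | 0.900, 0.950 | 0.08 (16%) | 0.11 (19%) |
| 10/2 | 0.875, 0.975 | 0.17 (32%) | 0.22 (39%) |

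Entry at month one instead of month two halves these values. In a simulation with Poisson counts (mean 1.65) and a t-test on raw counts, two-sided type I error was 4.5% for 6/6 and 8.4% for 10/2. At the extreme of 12/0 it was 13.5%, with a false difference of 0.25.

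**A milder scenario.** If drop-out is spread evenly over four months, about 6 of the 12 fall in the window and enter near month one on average. Even with a 5/1 split, the false difference is 2.22 × (4 × 0.25) / 40 = 0.056, about 10% of 0.57.

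**The case against.** The strongest reply concerns allocation. A reader might infer that a newcomer simply takes the vacated place and hence a known arm, so that selection bias is built in. The protocol does not say this. The replacement rule directly follows the description of eligibility check, MMSE, stratum and individual randomisation. Methods and design gives the same rule, and Group assignment has an independent researcher use a list. None of them makes an exception for late entrants. If that rule applies, replacements split evenly in expectation whichever arm the drop-outs left, and the false difference is zero in expectation. This stands: the allocation point is an ambiguity, not a stated non-random procedure.

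The 10/2 case is also close to a worst case, since it needs all 12 drop-outs to leave within two months, most of them from one arm, and to be replaced at the last permitted moment. Higher drop-out in the sensor arm is possible but not shown. Most exit routes are neutral between arms, and Possible harms lets intervention residents with system problems switch to standard care. This stands too.

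The protocol does not commit to raw counts. It also lists regression and multilevel models, which can carry an exposure term, and such detail may sit in an analysis plan not shown. The missing offset is therefore no finding in itself. Nor do inflation to 80 and early replacement contradict each other, since the margin can cover losses after month two.

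None of this removes the rule that permits entry until halfway through a four-month period. A reading in which each late entrant gets four full months would remove the exposure problem, but no section says so.

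**Conclusion.** The point holds in a limited form. The stated replacement rule, read with the four-month period, allows follow-up of as little as half the planned length, in a trial sized on mean falls per person. For a comparison of counts, this dilutes the difference even under balanced replacement: 0.52 to about 0.48 with 6 month-two replacements in each arm of 40.

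Bias between arms is conditional. It is zero for a balanced split, and about 0.1 to 0.2 falls for 8/4 to 10/2 splits of 12 replacements all entering at month two; it is smaller with earlier entry or fewer replacements. These sizes rest on assumed splits, on assumed entry times, and on treating the planning means as falls per four months. The documents do not support the conclusion that the comparison is biased as planned, or that replacements are allocated outside the randomisation. It remains worth settling before recruitment, because the trial is open and the remedy is cheap.

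**What to change.** Amend the replacement rule and the analysis text as follows.

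1. Every late entrant is stratified by MMSE and allocated by the next unused entry of the randomisation list, never to the vacated arm.
2. State how long late entrants are followed: to the end of the running system test period, or for four months of their own.
3. Analyse falls per person-time, using a count model with the log of time at risk as offset. Keep drop-outs' observed data as far as consent allows, since Data management requires all data to be removed when consent is withdrawn.
4. Report the number and entry time of late entrants by arm, and repeat the primary analysis without them.

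The cost is about one paragraph and one model term. Allocating from the list may leave the arms slightly unequal in size, which is a small price for keeping the comparison randomised. The offset corrects for unequal observation time; it would not repair non-random allocation, so item 1 is needed in its own right.
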